## Abstract

**Background:**

Hip fractures are a common type of fragility fracture that afflict 293,000 Americans (over 5,000 per week) and 35,000 Canadians (over 670 per week) annually. Despite the large population impact the optimal fixation technique for low energy femoral neck fractures remains controversial. The primary objective of the FAITH study is to assess the impact of cancellous screw fixation versus sliding hip screws on rates of revision surgery at 24 months in individuals with femoral neck fractures. The secondary objective is to determine the impact on health-related quality of life, functional outcomes, health state utilities, fracture healing, mortality and fracture-related adverse events.

**Methods/Design:**

FAITH is a multi-centre, multi-national randomized controlled trial utilizing minimization to determine patient allocation. Surgeons in North America, Europe, Australia, and Asia will recruit a total of at least 1,000 patients with low-energy femoral neck fractures. Using central randomization, patients will be allocated to receive surgical treatment with cancellous screws or a sliding hip screw. Patient outcomes will be assessed at one week (baseline), 10 weeks, 6, 12, 18, and 24 months post initial fixation. We will independently adjudicate revision surgery and complications within 24 months of the initial fixation. Outcome analysis will be performed using a Cox proportional hazards model and likelihood ratio test.

**Discussion:**

This study represents major international efforts to definitively resolve the treatment of low-energy femoral neck fractures. This trial will not only change current Orthopaedic practice, but will also set a benchmark for the conduct of future Orthopaedic trials.

**Trial registration:**

The FAITH trial is registered at ClinicalTrials.gov (Identifier NCT00761813).

## Background

Hip fractures are a common type of fragility fracture that afflict 293,000 Americans (over 5,000 per week) and 35,000 Canadians (over 670 per week) annually [1,2]. The prevalence of hip fractures is likely to exceed 500,000 annually in the United States and 88,000 in Canada over the next 40 years [3,4]. The estimated annual health care costs will reach a staggering $17 billion in the United States [5] and $650 million in Canada [6,7]. Hip fractures are associated with a 30% mortality rate at 1 year [8] and profound temporary and sometimes permanent impairment of independence and quality of life [9,10]. The disability-adjusted life-years lost as a result of hip fractures ranks in the top 10 of all cause disability globally [3].

Intracapsular fractures (also known as femoral neck fractures) may be either undisplaced or displaced. Internal fixation, in which a mechanical implant fixes the two segments of bone together, is the best way to manage undisplaced fractures [11] and, depending on patient characteristics and surgeon preference, can be used to manage displaced fractures as well [12].

Complications of internal fixation include avascular necrosis of the femoral head as well as early implant failure and nonunion [13,14]. Approximately 30% of surgically treated hip fractures require revision surgery [15-17]. These revisions are associated with a large burden of morbidity and appreciable mortality. Even patients who do not require revision surgery may have long term functional limitation due to soft tissue damage at the time of surgery.

The most popular approaches to internal fixation include multiple cancellous screws or a single compression screw and side plate (i.e., sliding hip screws). Both approaches have strong physiologic rationale and ardent advocates; however, there is no consensus regarding the optimal approach for management of intracapsular hip fractures [12].

### Multiple cancellous screws

Advocates of multiple cancellous screws focus upon its superior torsional stability, limited disruption of femoral head blood supply, and minimally invasive insertion [18-22]. Based on physiologic and observational studies, most surgeons use 3 parallel cancellous screws in a triangular (typically inverted) orientation [12,20]. Proponents of cancellous screws further argue that small diameter screws retain more viable bone after insertion compared to the larger sliding hip screws [18-22]. Retaining more cancellous bone optimizes vascularity and thus may reduce the risk of avascular necrosis of the femoral head. A randomized controlled trial (RCT) comparing 3 cancellous screws with a larger sliding hip screw found 3.5-fold greater femoral head vascularity at follow-up bone scanning with screws [22]. Surgeons can insert cancellous screws using 3 small stab incisions with limited blood loss and operating time. This minimally invasive approach may limit damage to the soft tissues around the hip and plausibly lead to better patient function and general wellbeing.

### Sliding hip screws

Despite the popularity of cancellous screw fixation, there is a strong biologic rationale supporting the use of sliding hip screws, a more biomechanically stable construct, in older patients with osteopenia or osteoporosis [23]. Cancellous screw fixation improves torsional strength; however, implant failures typically occur with bending and vertical shear loads (i.e., with weight-bearing). The sliding hip screw, the gold standard approach in treating inter-trochanteric fractures of the hip, has gained popularity as an alternative in the management of femoral neck fractures. Proponents of the sliding hip screw believe its superior biomechanical properties and greater fracture stability in osteoporotic bone should decrease the need for revision surgery. Sliding hip screw constructs have shown 2-fold greater maximal strength and less displacement under physiologic loading conditions compared to cannulated screws. In a cadaveric model, the sliding hip screw performed better than cancellous screws in stabilizing unstable femoral neck fractures under cyclic loading [21]. The sliding hip screw performed better in osteoporotic bone and was less sensitive to decline in bone mineral density than screws [21]. Newer minimally invasive techniques allow sliding hip screws to be inserted with small incisions and smaller side plates with limited blood loss and operating times [24].

### Inconclusive clinical evidence

Bhandari and colleagues conducted a systematic review and meta-analysis comparing arthroplasty to internal fixation in patients with displaced femoral neck fractures. Results demonstrate that while it may increase surgical mortality, arthroplasty reduced the need for revision surgery (RR = 0.23, 95%; CI: 0.13-0.42, homogeneity p < 0.01) [16]. The authors conducted a sensitivity analysis to explore reasons for variability and found that arthroplasty, compared to internal fixation, appeared to decrease the risk of revision far more when the method of internal fixation was screws alone (RR = 0.11) than when the method of internal fixation was a compression screw and side plate (RR = 0.59) (p < 0.01 for difference in estimates).

A meta-analysis by Parker and colleagues evaluated 28 trials (N = 5547 patients) and reported no advantage of any internal fixation technique over any other technique [25]. The trials were small (range in sample sizes: 33 to 410), and methodologically limited. Only 5 RCTs evaluated sliding hip screws versus cancellous screws (4 displaced femoral neck fractures, 1 undisplaced femoral neck fractures). These trials ranged in size from 33 to 209 patients and had few total outcome events (range: 3–34 events). When the data from these 5 studies were pooled, the point estimate trended toward favouring sliding hip screws compared to cancellous screws; however, the difference was not statistically significant.

In summary, both direct comparisons between sliding hip screws and cancellous screws and indirect comparisons (comparing sliding hip screws and cancellous screws separately to arthroplasty) suggest a possible benefit for a sliding hip screw over multiple cancellous screws in reducing the need for revision surgery. The indirect nature of the comparison from the meta-analysis of arthroplasty versus internal fixation, and the small sample sizes, methodological limitations, and non-significant pooled estimates from the direct comparisons, leaves the issue very much in doubt.

### Surgical management of hip fractures

Bhandari and colleagues contacted 442 surgeons in an international survey [12] to explore surgeons’ opinions regarding internal fixation for femoral neck fractures. For undisplaced femoral neck fractures, 92% of surgeons preferred internal fixation. Despite the evidence suggesting the superiority of sliding hip screws, 90% of surgeons preferred cancellous screws. In displaced hip fractures, 25% of surgeons preferred internal fixation when compared with arthroplasty; and of those who preferred internal fixation, 68% preferred cancellous screws.

## Methods/Design

### Pilot and vanguard phase

We have successfully completed a pilot RCT (n = 80 patients) to assess the feasibility of the definitive FAITH trial. The primary outcomes of the pilot study were the rates of reoperation at 24 months to promote fracture healing, relieve pain, treat infection, treat a peri-prosthetic fracture, or improve function. We also collected functional outcomes on all patients. Our pilot RCT demonstrated: (1) our ability to recruit patients for the definitive trial; (2) investigator compliance with key aspects of the protocol; (3) maintenance of data quality; (4) maintenance of high follow-up rates; (5) our ability to organize trial procedures in a multinational trial; and (6) overall event rates for our primary outcome that support our sample size calculation. We have also used the vanguard phase to optimize case report forms and a manual of operations. To avoid a break in funding and to maintain our momentum across recruiting sites, the Vanguard phase transitioned into the definitive trial phase without stopping. The rationale for the definitive FAITH trial is supported by: (1) the substantial burden of hip fracture injuries to both patients and the healthcare system; (2) differences in the surgical management of hip fractures; (3) a lack of clinical evidence to inform the optimal method of internal fixation; (4) the demonstrated success of the pilot RCT.

### Study objectives

The primary objective of the FAITH study is to evaluate the effects of sliding hip screws versus cancellous screws on revision surgery at 24 months post-injury. The secondary objectives are to determine the impact of sliding hip screws versus cancellous screws on health-related quality of life, functional outcomes, health state utilities, fracture healing, mortality, and other adverse events such as avascular necrosis, nonunion, malunion, implant breakage or failure, and infection.

### Study design

FAITH is a multi-centre, concealed RCT using minimization to determine patient allocation. We will randomly assign a minimum of 1,000 patients who have sustained a femoral neck fracture to one of two treatment groups. The first treatment group involves fixation of the fracture with multiple small diameter cancellous screws (i.e., cancellous screw group). The second treatment group involves fixation of the fracture with a single larger diameter screw with a side plate (i.e., sliding hip screw group). We hypothesize that sliding hip screws will have lower rates of re-operation (primary outcome) and higher functional outcome scores (secondary outcome) at 24 months when compared with cancellous screws. The FAITH trial is registered at ClinicalTrials.gov (Identifier NCT00761813) and has received McMaster University Research Ethics Board approval (REB#: 06–402) and approval from local ethics boards.

### Randomization

We will randomize patients using minimization to ensure balance on baseline covariates An automated Internet-based randomization system centralized at the FAITH Methods Centre at McMaster University, which we have used successfully for other multicenter trials, will ensure concealed randomization of eligible consenting patients. Concealed randomization will be ensured through two strategies: 1) the randomization sequence will be predetermined by research personal who are external to the clinical sites who are determining patient eligibility; and 2) the internet-based randomization system will require surgeons to enter patients into the trial before treatment allocation is divulged. Minimization will be used to ensure balance between intervention groups for several patient factors. The minimization approach takes into account each pre-identified prognostic variable and sums over the variables to allocate each patient to the treatment that minimizes the current differences between groups for those prognostic variables. Unlike stratified randomization, minimization works toward minimizing the total imbalance for all factors together instead of considering mutually exclusive subgroups (strata) [26]. Based upon our international survey of surgeons [12] and current evidence [27], we will minimize for the following prognostic factors: (1) Age (i.e., 50–80 years or >80 years (81 years or older)); (2) Undisplaced or displaced femoral neck fractures; (3) Pre-fracture living setting (i.e., institutionalized or not institutionalized); (4) Pre-fracture functional status (i.e., using ambulatory aid or independent ambulator); (5) American Society for Anesthesiologists (ASA) Class (i.e., Class I/II or III/IV/V) [28]; and (6) Centre.

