### Eligibility criteria

Eligible patients will meet all the following inclusion criteria: (1) Men or women aged 50 years and older (with no upper age limit); (2) Fracture of the femoral neck confirmed with anteroposterior and lateral hip radiographs, computed tomography, or magnetic resonance imaging (MRI); (3) Operative treatment of displaced fractures within 4 days of presenting to the emergency room, or operative treatment of undisplaced fractures within 7 days of presenting to the emergency room; (4) Patient was ambulatory prior to fracture, though they may have used an aid such as a cane or a walker; (5) Anticipated medical optimization for operative fixation of the hip; (6) Provision of informed consent by patient or a legally appointed representative; (7) No other major trauma (defined as an Injury Severity Score >16); and (8) Low energy fracture, in the judgment of the attending surgeon.

We will exclude patients meeting any of the following criteria: (1) Patients not suitable for internal fixation (i.e., severe osteoarthritis, rheumatoid arthritis, or pathologic fracture); (2) Associated major injuries of the lower extremity (i.e., ipsilateral or contralateral fractures of the foot, ankle, tibia, fibula, knee, or femur; dislocations of the ankle, knee, or hip; or femoral head defects or fracture); (3) Retained hardware around the affected hip; (4) Infection around the hip (i.e., soft tissue or bone); (5) Patients with disorders of known bone metabolism except osteoporosis (i.e., Paget’s disease, renal osteodystrophy, osteomalacia); (6) Patients with a history of frank dementia that would interfere with assessment of the primary outcome (i.e., revision surgery at 24 months); (7) Likely problems, in the judgment of the investigators, with maintaining follow-up (i.e., patients with no fixed address, report a plan to move out of town, or intellectually challenged patients without adequate family support); and (8) Exclusion of a patient because of enrolment in another ongoing drug or surgical intervention trial will be left to the discretion of the attending surgeon, on a case-by-case basis.

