### Statistical plan

#### *Sample size determination*

The determination of sample size is based upon a comparison for the primary outcome (revision surgery) of the sliding hip screw versus multiple cancellous screw groups. All statistical hypotheses will be assessed using 2-sided significance tests. Alpha levels of 0.05 have been chosen for the primary and 0.01 for the secondary outcomes. Previous studies have reported revision surgery rates in hip fracture patients that have ranged from 0-44% [39-41], with a weighted pooled risk of 22.7% (95% CI: 19.6-25.8%). In a pooled estimate of 5 RCTs comparing sliding hip screw fixation with multiple screw fixation in patients with displaced or undisplaced hip fractures, sliding hip screws reduced the risk of revision by 32% (95% CI: 3-53%, p = 0.04, Q = 5.3) [22,42-45]. The sample size calculation reflects the proposed primary analysis, which will use the Cox proportional hazards model, and is based on methods described by Collett [46]. The goal is to calculate the required number of patients that will yield a sufficient number of outcome events (revision surgeries) in order to have adequate statistical power for a given size of treatment effect. This was done by taking into account the anticipated revision surgery rates in the multiple cancellous screw group, the postulated relative risk reduction with sliding hip screws, and the rates of mortality and loss to follow-up. Because some of these inputs are expected to change over the two year period of follow-up, the expected number of person-years of follow-up and the expected numbers of study events in each group were calculated initially for the first year of follow-up (year 1). The calculations were then repeated for the second year of follow-up (year 2), after having estimated the number of patients in each group who would survive, be event-free, and available for continued follow-up at 12 months post-randomization.

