### Statistical methods

#### *Primary analysis*

All outcome analyses will adhere to the intention to treat principle. To evaluate the effect of sliding hip screw versus cancellous screws in time to revision rates, a Cox proportional hazards model will be used with the following covariates that are included in the minimization procedure: (1) Age (50–80 years or >80 years (81 years or older)); (2) Undisplaced or displaced femoral neck fractures; (3) Pre-fracture living setting (i.e., institutionalized or not institutionalized); (4) Pre-fracture functional status (i.e., using ambulatory aid or independent ambulator); (5) American Society for Anesthesiologists (ASA) Class (i.e., Class I/II or III/IV/V); and (6) Clinical site.

The treatment effect will be evaluated using a likelihood ratio test, and the validity of the proportional hazards assumption of the Cox model will be assessed. Survival rates at each follow-up period will be compared and then the overall difference between survival curves with log-rank tests will be evaluated, adjusting for the covariates. Absolute revision rates, risk reduction, absolute risk reduction, and the number needed to treat with screws and sideplate will be calculated. All results will be presented with 95% confidence intervals.

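### Age enters the primary Cox model only as 50–80 versus over 80; this is valid, but an added age-in-years term could recover a little power if revision risk varies within the two bands

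*Protocol article*

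**What the plan says.** The Eligibility criteria admit "Men or women aged 50 years and older (with no upper age limit".

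Under Randomization the article states that "we will minimize for the following prognostic factors" and lists six factors. The first is age in two bands, "1) Age (i.e., 50–80 years or >80 years (81 years or older".

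Under Primary analysis, "a Cox proportional hazards model will be used with the following covariates that are included in the minimization procedure". Age appears there in the same two bands, "Age (50–80 years or >80 years (81 years or older", and no finer age term is mentioned. The test is also fixed: "The treatment effect will be evaluated using a likelihood ratio test".

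Age is therefore described as prognostic. The article gives neither the size nor the shape of any relation between age and revision surgery.

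**The concern.** Minimisation needs categories; a regression model does not. With entry from 50 and no upper limit, the lower band spans about 30 years and the upper band is open-ended. The planned model gives patients aged 50 and 80 the same age-related hazard, and likewise patients aged 81 and 100.

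If the hazard of revision changes with age inside a band, that variation is left out of the model. In a Cox model, leaving out prognostic variation draws the treatment log hazard ratio towards zero compared with the value conditional on age. The standard error hardly changes, so some power is lost.

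What is at stake is a small amount of efficiency in the primary test, in a trial whose target fell from 1,500 to 1,000 patients. Validity is not at stake.

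**Working it through.** **1. The plan's own power figure.** Inputs are from Sample size determination: 500 per group; revision 15.5% (year 1) and 27.2% (year 2); mortality 11.0% and 18.2%; loss 12.2% and 5.9%; two-sided alpha 0.05; relative risk reduction 30%. Each annual rate p becomes a hazard −ln(1−p), with death and loss as competing exits.

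- Cancellous screws, year 1: revision hazard 0.168, total exit hazard 0.415, so P(revision) = (0.168/0.415) × (1 − e^−0.415) = 0.138, and 0.660 remain. Year 2: hazards 0.317 and 0.579, so P = 0.241. Two-year total: 0.138 + 0.660 × 0.241 = 0.297.
- Sliding hip screw (rates × 0.7), year 1: hazards 0.115 and 0.361, so P = 0.096, and 0.697 remain. Year 2: hazards 0.211 and 0.473, so P = 0.168. Total: 0.096 + 0.697 × 0.168 = 0.214.
- Events: 500 × (0.297 + 0.214) ≈ 255.
- Hazard ratio: ln(1 − 0.1085)/ln(1 − 0.155) = 0.682.
- Power: Φ(√(255/4) × |ln 0.682| − 1.96) = Φ(1.10) ≈ 86.4%, against 86.3% in Table 3.

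The stated power is thus reproduced with no covariate in the calculation. It does not depend on how age is coded.

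**2. What finer age would add.** Three separate simulations used 1,000 patients and rates close to those above. Age distributions and age gradients are assumptions.

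- **A:** over-80 indicator alone versus indicator plus age in years; true treatment hazard ratio 0.70; age about 74 (SD 12); 2,500 runs.
- **B:** over-80 indicator versus linear age in its place; true hazard ratio 0.682; age mean 72 (SD 12) or 78 (SD 10); 4,000 runs.
- **C:** the same nested comparison as A; true hazard ratio 0.70.

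Gain in power, percentage points:

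| Age effect on revision | A | B | C |
|---|---|---|---|
| None | – | – | about 0 |
| HR 1.1 per decade | – | about 0 | – |
| HR 1.2 per decade | 0.2 (80.4 to 80.6%) | 0.1 | 0.5 |
| HR 1.5 per decade | 0.5 (78.7 to 79.2%) | 0.4 to 1.0 | 1.1 |
| HR 1/1.5 per decade | 1.2 (79.8 to 81.0%) | – | – |
| HR 2.0 per decade | 3.3 (73.4 to 76.7%) | 1.7 to 2.6 | 2.7 |
| Step at 80 | – | −0.2 | about 0 |
| Inverted U | – | −0.1 | – |

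The Monte Carlo standard error of the gain in A is 0.3 to 0.5 points, so its gain at 1.2 cannot be told from zero. With a lower year-2 revision rate (13.8%), A gave 0.3, 0.7 and 2.4 points at 1.2, 1.5 and 2.0.

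**3. Treatment estimate.** In B (true 0.682), the mean hazard ratio moved from 0.683–0.685 to 0.680–0.683 at 1.5 per decade, and from 0.687–0.689 to 0.680–0.681 at 2.0. In A at 2.0 per decade, the mean log hazard ratio moved from −0.342 to −0.353 (true −0.357), which is 0.710 to 0.703 against 0.700.

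**4. Type I error.** It was 5.4% under both models in A, and 5.3% (two-level) versus 4.9% (linear) in B.

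**The case against.** The strongest reply is that nothing here is an error. The two sections agree with each other, and adjusting for minimisation factors in the form used for allocation is accepted practice. That stands, and it is why this is only an optional refinement.

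Second, the loss is conditional. A reader might infer from the word prognostic that power and the estimate are reduced as a matter of fact. The documents do not support that, because they give no gradient within the bands. Without one, or with a step at 80, there is nothing to gain.

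Third, the larger gains need the hazard to double with each decade, which nothing in the article suggests. The simulations also leave out displacement, living setting, ambulatory status, ASA class and site. Where these correlate with age they would absorb part of its effect, so the gains are probably overstated. Both points stand.

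Fourth, the attenuation is non-collapsibility: the two models target slightly different conditional hazard ratios. That is right, and the shift should not be called bias in the planned estimate.

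One part of the reply does not carry. The small negative results for a step and an inverted U come from simulation B, where linear age replaced the indicator, and they lie within simulation error. Adding age to the indicator still captures a step at 80, and C showed a change of about zero there.

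**Conclusion.** The point holds as a minor, conditional improvement. The article fixes age as a two-level factor in the primary model although a finer value must already be known. If revision risk varies with age inside the bands, the planned model may give up about 0 to 1 point of power for age hazard ratios up to 1.5 per decade and roughly 2 to 3 points at 2.0. It gives up nothing if the effect is a step at 80. The treatment hazard ratio shifts by 0.003 or less up to 1.5 per decade, and by at most about 0.008 at 2.0. These sizes rest on assumed age distributions and gradients, and on simulations without the other covariates.

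A reader might also infer that, because age could predict death and death censors revision, the two-level coding makes censoring informative. The article reports no relation between age and death, no resulting bias was quantified, and the model already includes ASA class, living setting and ambulatory status. That reading is not supported and forms no part of this point. The planned analysis is valid and no stated sample size or power figure changes.

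**What to change.** Leave the minimisation as it is. In Primary analysis, keep the over-80 indicator, because it is an allocation factor, and prespecify age in years as one added linear term in the Cox model. Name any spline form as a sensitivity analysis, so that the primary model has a single fixed specification. Settle this before any comparison between the arms is seen.

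The cost is one line of text and one degree of freedom against roughly 255 expected events. No new data and no extra patients are needed.
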